**FIGURE 3 F3:**
[figure not shown]
Integration of clinical diagnostics and study procedures in the work-up before **(A)** and the follow-up after **(B)** AF ablation. Procedures in white are standard clinical procedures, procedures in black are added for research purposes. *When applicable (in case of epicardial or hybrid ablation). AF, atrial fibrillation; BMI, body mass index; CMR, cardiac magnetic resonance imaging; CT, computed tomography; ECG, electrocardiogram; extECG, extended surface electrocardiogram; LAA, left atrial appendage; MoCa, Montreal Cognitive Assessment.

#### Study Procedures During Pre-ablation Work-Up

For ISOLATION study participants, the standard pre-AF ablation work-up is combined with the following baseline study procedures: determination of body composition, extended surface ECG (extECG), analysis of biomarkers and common gene variants, questionnaires, and characterization of AF patterns (Figure 3A, study procedures in black). For ISOLATION “light” registry participants the study procedures are limited to analysis of biomarkers, common gene variants, and questionnaires.

Both the clinical facets and research aspects of the pre-ablation work-up are overseen by a case manager. The case manager educates patients on the AF ablation procedure and study participation, coordinates study procedures, notifies abnormalities in results of diagnostic tests, and provides patients with information on logistics and planning.

### Atrial Fibrillation Ablation

AF ablation comprises pulmonary vein isolation (PVI) with or without additional lesions. The type of ablation that is performed is determined in a multidisciplinary team meeting and depends on the patient’s preference and characteristics. The choice of ablation strategy is not influenced by study participation. In the participating centers, first ablations for paroxysmal AF and for persistent AF with normal to modestly dilated atria or in elderly patients are usually performed by cryoablation (Figure 2). First ablations for persistent AF with advanced atrial dilation or with concomitant atrial flutter or atrial tachycardia are mostly performed by wide atrial circumferential ablation (WACA) using radiofrequency applications, if needed complemented with cavo-tricuspid isthmus ablation (in case of typical atrial flutters). Patients with longstanding persistent AF (> 1 year) are usually treated with thoracoscopic or hybrid AF ablation. Patients with recurrent AF undergoing a second (redo) procedure are mainly treated with radiofrequency ablation or thoracoscopic/hybrid AF ablation, whereas for third or further procedures hybrid procedures are recommended, if patients are suitable candidates and no earlier hybrid treatment was performed. Patients with an indication for cardiac surgery and known AF are discussed in an arrhythmia team and considered for concomitant epicardial AF ablation. Treating physicians may choose to deviate from these recommendations depending on specific patient characteristics and patient preference. All patients planned to undergo an endocardial procedure are treated with oral anticoagulants around the ablation (3). In addition, a transesophageal echocardiogram is performed prior to all endocardial procedures to exclude intracardiac thrombi.

#### Study Procedures During Atrial Fibrillation Ablation

Whether additional, optional study procedures are performed during the procedure depends on the type of ablation selected (Figure 3B). If endocardial electroanatomical mapping is performed during the ablation procedure, these data may be used for additional offline analyses. In the case of hybrid or concomitant epicardial ablation, additional epicardial mapping, and left atrial appendage (LAA) biopsies may be performed (Supplementary Material 1).

### Post-ablation Follow-Up

After the ablation procedure, patients return to the outpatient clinic at 3 and 12 months and have scheduled teleconsultations after 6 and 24 months. Prior to the contacts at 6, 12, and 24 months, a 48-h Holter recording is performed. 12-lead ECGs are obtained during every on-site follow-up visit. In addition, patients receive an on-demand 7-day prescription for the use of the smartphone application FibriCheck (Qompium, Hasselt, Belgium) prior to all scheduled consultations. FibriCheck is an app that uses photoplethysmogram (PPG) signals to assess heart rate regularity and symptom-rhythm correlation (13). Patients are instructed to measure 3 times per day and in the case of symptoms, in accordance with the TeleCheck-AF approach (14). If irregularity of the heartbeat is detected and AF is suspected, additional or longer Holter recordings may be performed to confirm AF recurrence by ECG documentation (Figure 3B, standard follow-up procedures in white).

#### Study Procedures During Post-ablation Follow-Up

For ISOLATION participants, on-site follow-up visits are complemented with the following study procedures: determination of body composition, extECG, and analysis of biomarkers. Questionnaires are repeated at 3, 12, and 24 months after the ablation (Figure 3B, study procedures in black). For ISOLATION “light” registry participants, study procedures are limited to the questionnaires.

### Short Description of Study Procedures

The rationale for the different study procedures is described in Supplementary Material 1, along with detailed descriptions of the procedures. A condensed version is provided here.

#### Determination of Body Composition

To explore the correlation between different anthropometric measures and ablation success, weight, fat percentage and lean body mass indices are estimated using bioelectrical impedance measurements obtained with body composition monitors. The results of these measurements are part of domain 1: clinical factors (Figure 1).

### Pre-procedural Rhythm Monitoring

To gain more insight into pre-ablation AF patterns, patients awaiting the AF ablation procedure receive a handheld patient-operated device which records single-lead ECGs. Patients are asked to record their heart rhythm three times a day during a maximum of 4 weeks. Additional registrations are recorded at each onset or relief of arrhythmia symptoms. Symptoms and their correlation to ECG recordings are documented in a patient diary. The obtained AF patterns are studied in domain 2 (Figure 1).

### Extended Surface Electrocardiogram

Detailed analysis of P-wave and fibrillation wave (F-wave) features from surface ECGs are increasingly used to characterize the degree of electrophysiological changes in the atria. In this study, unfiltered extECGs using a total of 21 leads will be recorded for up to 5 min to allow for signal-averaged analyzation of P-waves (for patients in sinus rhythm) and for examination of F-wave frequency and complexity (for patients in AF). The results are a component of domain 4: electrophysiological characteristics (Figure 1).

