**FIGURE 1 F1:**
[figure not shown]
The 6 domains of interest in which predictors for successful atrial fibrillation ablation are sought: (1) clinical risk factors, (2) pre-procedural AF patterns, (3) anatomical characteristics, (4) electrophysiological characteristics, (5) circulating biomarkers, and (6) genetic background. AF, atrial fibrillation; CT, computed tomography; ECG, electrocardiogram; MRI, magnetic resonance imaging. Study procedures with an asterisk are conducted for a subset of patients.

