### Statistical Considerations

Data analyses will be performed with SPSS Statistics, version 25.0 or higher (IBM SPSS Inc., Chicago IL). Baseline data will be presented by count (percentage) for categorical variables and compared using the Chi-square test. Continuous data will be presented as means (± standard deviation) or medians (interquartile range) and compared using the independent samples *t*-test or Mann-Whitney *U*-test. Missing data will be estimated using multiple imputation by chained equations. Uni- and multivariable regression analyses will be performed to analyze the relation of dependent variables with the primary and applicable secondary endpoints. The secondary endpoints time to recurrence of atrial arrhythmia and AF will be assessed using Cox proportional hazard regression. All endpoints will be assessed using a level of significance of α = 0.05.

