#### Development of Prediction Model and Sample Size Calculation

An exploratory multimodality model will be created to predict the primary endpoint (ablation success). Ideally, to develop a reliable prediction model all variables of interest that will be studied in the model should be defined prior to the data collection. However, this study includes several relatively new techniques, which each provide a multitude of possible variables of interest for which the predictive value has not been established. Defining variables to be included in the model up-front could limit its eventual predictive value, as the predefined variables might not prove to be the most discriminative variables. Therefore, an exploratory analysis of variables in the following categories will be performed first (Figure 1): (1) clinical risk factors, (2) pre-procedural AF patterns, (3) anatomical characteristics, (4) electrophysiological characteristics, (5) circulating biomarkers, and (6) genetic background. For subcategory 1–5 the three variables with the strongest correlation to ablation success are selected and presented to the model. For subcategory 6 the two strongest predictors are used. The ablation technique that is chosen is used as a separate predictor. This approach leads to a total of 18 variables used to develop the multimodality model. To ensure sufficient power to explore these 18 variables, a total of 180 events is required to conform to the rule-of-thumb to aim for 10 events per variable. When assuming an event rate of 32% (68% successful AF ablations) (4, 5), inclusion of 563 patients is required to achieve sufficient events. Accounting for a lost-to-follow-up rate of 15%, the aim is to include 650 patients scheduled for first catheter ablation.

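### P-wave and F-wave features are observed in different patients at baseline, yet the plan ranks them in one pool for one model, with an unqualified imputation rule

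*Protocol article*

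**What the plan says.** Protocol article, Extended Surface Electrocardiogram: the recording is used for "signal-averaged analyzation of P-waves (for patients in sinus rhythm) and for examination of F-wave frequency and complexity (for patients in AF". Both feature types share one domain: "The results are a component of domain 4: electrophysiological characteristics (Figure 1".

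Development of Prediction Model and Sample Size Calculation: "For subcategory 1–5 the three variables with the strongest correlation to ablation success are selected and presented to the model". This section describes one logistic model, built by forward selection with AIC as the stopping rule. Performance is examined in the whole cohort and by ablation strategy. Rhythm at recording is named neither as a predictor nor as a stratum.

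Statistical Considerations: "Missing data will be estimated using multiple imputation by chained equations". No exception is given for features that cannot be measured in the rhythm present at the recording.

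Atrial Fibrillation Ablation: the treated population runs from paroxysmal to longstanding persistent AF, so both rhythms should be expected at the baseline visit.

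**The concern.** Whether a P-wave or an F-wave feature is available is decided by the rhythm at the recording. That rhythm plausibly follows AF type and so prognosis. The plan treats all domain-4 candidates as if they were measured in the same people. Three steps then become doubtful: the ranking, the treatment of the absent values, and the AIC comparison of candidate models.

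The extended ECG is one of the study's new techniques, and the model is meant to support decisions for individual patients. A domain-4 choice driven by who happened to be in which rhythm, or by the imputation model, would weaken that part of the result.

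**Working it through.** **Inputs from the article** (Development of Prediction Model and Sample Size Calculation): three variables from each of domains 1 to 5; for domain 6, "For subcategory 6 the two strongest predictors are used"; and "The ablation technique that is chosen is used as a separate predictor". Also 10 events per variable, a 32% event rate, 15% loss to follow-up and 650 patients.

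**Inputs assumed:** the share *a* of patients in AF at the baseline recording (20%, 35%, 50%) and the same 32% event rate in both rhythms. The article gives neither.

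**1. The plan's own figure.**
- Variables: 5 × 3 + 2 + 1 = 18. Events: 18 × 10 = 180. Patients: 180 / 0.32 = 562.5, so 563.
- Allowing for loss: 563 × 1.15 = 647.5 (648), or 563 / 0.85 = 662.4 (663). The stated 650 is within about 2% of either.
- Expected at 650: 650 × 0.85 = 552.5, taken as 552 evaluable patients; 552 × 0.32 = 176.6, about 177 events; 176.6 / 18 = 9.8 per variable.

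This count treats every candidate as available in every evaluable patient.

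**2. What is observed for each feature type.** P-wave events = 552 × (1 − *a*) × 0.32. F-wave events = 552 × *a* × 0.32.

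| Assumed share in AF | P-wave: patients / events | F-wave: patients / events | Both types at one recording |
|---|---|---|---|
| 20% | 442 / 141 | 110 / 35 | 0 |
| 35% | 359 / 115 | 193 / 62 | 0 |
| 50% | 276 / 88 | 276 / 88 | 0 |

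So 20% to 50% of P-wave values and 50% to 80% of F-wave values would be absent because of rhythm alone. The zeros in the last column do not depend on the assumed share.

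**3. Ranking on observed values.** P-wave correlations come from patients in sinus rhythm and F-wave correlations from patients in AF. Their precision differs too. The standard error of a null correlation is about 1/√n, which at 20% in AF is 1/√442 = 0.048 against 1/√110 = 0.095. Choosing the largest correlation then favours, by chance, the type seen in fewer patients.

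**4. Modelling, under each reading of the imputation rule.**
- *Absent values are imputed.* No baseline record holds both types, so nothing in the data informs their association given the other variables. The imputation model supplies it. The P-wave coefficient then also draws on patients in AF, whose values were generated from the relation seen in sinus rhythm, and the reverse holds for F-waves.
- *Absent values are not imputed.* A model with one feature of each type has 0 complete cases. A model with only one type is fitted in one rhythm only. AIC values are comparable only for models fitted to the same patients; at 20% in AF a P-wave candidate would be fitted in 442 patients and an F-wave candidate in 110.

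**The case against.** The strongest reply is that this is a condensed article. The imputation sentence is general, and nothing says that a P-wave feature in a patient recorded in AF counts as missing data. The text does not say in which patients the correlations are computed, or whether imputation comes before ranking. Domain 4 also draws on the standard 12-lead ECG (Discussion), so a rhythm-dependent feature might never be selected. Interaction terms are foreseen, and the model is called exploratory.

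Much of this stands. A reader might infer that the plan explicitly imputes these features; it does not say so. What the reply does not remove is that the article itself fixes the pool, the ranking rule, the number selected, the model, the stopping rule and the imputation method, and these do not fit together under either reading above. The interaction provision gives left atrial volume index or AF type with ablation technique as examples; rhythm at recording is not among them.

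Other stronger readings also lack support:
- *That imputed values could not exist.* The cohort includes paroxysmal AF. Such a patient, if in AF at the visit, has P-waves at other times, so the value is unobserved at that recording rather than impossible. Extended ECGs are repeated at on-site follow-up visits, so some patients may show both rhythms over time, but those recordings follow ablation and are not baseline predictors.
- *That mapping and biopsy data raise the same problem in the main model.* The article says "Whether additional, optional study procedures are performed during the procedure depends on the type of ablation selected" and, under Figure 1, "Study procedures with an asterisk are conducted for a subset of patients". But these procedures are optional, invasive characterization is listed as a substudy area, and the Discussion describes the ECG-derived electrophysiological predictors as non-invasive. Nothing places mapping or biopsy variables in the main model.
- *That the final model could not be used in the other rhythm.* This would follow only if such a feature survived both the ranking and the AIC selection.

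**Conclusion.** The point holds as a conflict between stated choices. Features from mutually exclusive rhythms are pooled, ranked together and offered to one model, and the imputation rule does not separate not measurable in this rhythm from not recorded. That the two types are never observed together at baseline follows from the text and needs no assumption. That the two subsets differ in prognosis is probable but not documented.

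The event counts (P-wave 141 to 88, F-wave 35 to 88, against 177 overall) are illustrative. They rest on an assumed 20% to 50% in AF and on equal event rates. If recurrence is commoner in patients recorded in AF, events shift from the P-wave to the F-wave column. The sample size arithmetic is not in dispute here. The plan should be changed before the domain-4 ranking is run, and no new data are needed.

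**What to change.** 1. Include rhythm at the baseline extended ECG as a predictor, and keep it in whenever a rhythm-dependent feature is in.
2. Enter each P-wave feature only through a sinus-rhythm × feature term and each F-wave feature only through an AF × feature term, with the value held constant in the other rhythm. Every candidate model is then fitted to the same patients, and AIC is comparable. Alternatively, do the domain-4 ranking and selection separately by rhythm.
3. Limit chained-equation imputation to values that were measurable in the recorded rhythm but were not recorded.

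The cost is wording in the analysis plan, slightly more coding and wider intervals for rhythm-specific terms. Rhythm as an extra variable makes 19 candidates, or 176.6 / 19 = 9.3 expected events each instead of 9.8. Carrying three features per rhythm would make 18 − 3 + 6 + 1 = 22, or 176.6 / 22 = 8.0. Splitting only the domain-4 step is preferable to a full 18-variable model within each rhythm, which at 50% in AF would have 88 / 18 = 4.9 events per variable.

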### Blood Samples

Blood for biomarker analyses is drawn at three separate time points during the study. Genetic analysis is performed on the blood drawn at baseline. Biomarkers of interest include inflammatory mediators, markers of myocardial wall stress, markers of fibrosis, markers of endothelial dysfunction and pro-thrombotic state, and markers for expression of genes regulating electrophysiological characteristics. The results are studied in domain 5: circulating biomarkers and 6: genetic background (Figure 1).

### Questionnaires

The following questionnaires are completed: Montreal Cognitive Assessment (MoCA), Toronto AF Severity Scale (AFSS), Atrial Fibrillation Effect on QualiTy-of-life (AFEQT), STOP-Bang, and a combined COPD questionnaire. Additional information on the questionnaires is provided in Supplementary Material 1.

### Additional Procedures for Substudies

Specific subsets of patients may be eligible to participate in a substudy of the ISOLATION study and/or ISOLATION “light” registry. Current areas of interest include cardiovascular imaging, non-invasive and invasive electrophysiological characterization, and concomitant comorbidities. Substudies that are currently actively enrolling patients and their primary objectives are listed in Supplementary Material 2. Patients eligible for participation in a substudy are asked for additional consent.

### Data Management

Patient identifiers are removed from study data, biological samples and recordings and replaced with a unique study number. Coded data is entered in a password-protected, secure electronic CRF [Castor EDC]. Raw data of procedures (e.g., extECGs) are stored under the respective patient identifier and will be available for further offline analysis. All information generated in this study will be considered confidential and is handled in according to the General Data Protection Regulation and the Dutch Act on Implementation of the General Data Protection Regulation. Monitoring is performed by the Clinical Trial Center Maastricht (CTCM) in accordance with the predefined monitoring plan and prevailing guidelines.

### Statistical Considerations

Data analyses will be performed with SPSS Statistics, version 25.0 or higher (IBM SPSS Inc., Chicago IL). Baseline data will be presented by count (percentage) for categorical variables and compared using the Chi-square test. Continuous data will be presented as means (± standard deviation) or medians (interquartile range) and compared using the independent samples *t*-test or Mann-Whitney *U*-test. Missing data will be estimated using multiple imputation by chained equations. Uni- and multivariable regression analyses will be performed to analyze the relation of dependent variables with the primary and applicable secondary endpoints. The secondary endpoints time to recurrence of atrial arrhythmia and AF will be assessed using Cox proportional hazard regression. All endpoints will be assessed using a level of significance of α = 0.05.

#### Development of Prediction Model and Sample Size Calculation

An exploratory multimodality model will be created to predict the primary endpoint (ablation success). Ideally, to develop a reliable prediction model all variables of interest that will be studied in the model should be defined prior to the data collection. However, this study includes several relatively new techniques, which each provide a multitude of possible variables of interest for which the predictive value has not been established. Defining variables to be included in the model up-front could limit its eventual predictive value, as the predefined variables might not prove to be the most discriminative variables. Therefore, an exploratory analysis of variables in the following categories will be performed first (Figure 1): (1) clinical risk factors, (2) pre-procedural AF patterns, (3) anatomical characteristics, (4) electrophysiological characteristics, (5) circulating biomarkers, and (6) genetic background. For subcategory 1–5 the three variables with the strongest correlation to ablation success are selected and presented to the model. For subcategory 6 the two strongest predictors are used. The ablation technique that is chosen is used as a separate predictor. This approach leads to a total of 18 variables used to develop the multimodality model. To ensure sufficient power to explore these 18 variables, a total of 180 events is required to conform to the rule-of-thumb to aim for 10 events per variable. When assuming an event rate of 32% (68% successful AF ablations) (4, 5), inclusion of 563 patients is required to achieve sufficient events. Accounting for a lost-to-follow-up rate of 15%, the aim is to include 650 patients scheduled for first catheter ablation.

Variables with possible interrelation (e.g., left atrial volume index or AF type with chosen ablation technique) will be tested for interaction and, if present, interaction terms will be included in the model. The model will be developed using logistic regression by forward selection with the use of the Akaike Information Criterion (AIC) as stopping rule. The discriminative performance of the model is evaluated by calculating the area under the receiver operator characteristic (AUROC) curve (C-statistic) and by comparisons of observed groups of different predictive frequencies. To assess the potential confounding effect of the ablation strategy that was chosen, performance analyses will be done for the entire cohort and separately for patients treated with different ablation strategies for sensitivity purposes.

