## Introduction

The prevalence of atrial fibrillation (AF) has risen substantially over the past decade, and it continues to rise due to the aging population and the increasing rate of concomitant risk factors and underlying structural heart diseases (1). AF is associated with an increased risk of ischemic stroke, developing and worsening of heart failure, and a significant symptom and financial burden (2). To maintain sinus rhythm and to decrease symptoms related to AF, catheter ablation is recommended in symptomatic patients (3). However, despite advanced ablation techniques and improved ablation outcomes over the last decade, about 30–50% of patients still experience recurrences of atrial arrhythmias within 1 year after the procedure (4, 5).

Although several readily available characteristics (including demographic information, established clinical AF risk factors, and left atrial volume) have previously been identified as predictors for AF ablation success, it remains challenging to estimate the success rate for an individual patient (6). A range of novel techniques estimating the extent of the atrial AF substrate has been proposed: to aid in the prediction of individual success rates biomarkers, such as inflammatory mediators and markers for fibrosis (7, 8), common gene variants associated with AF, and non-invasive electrophysiological characteristics recorded on surface electrocardiograms (ECG) (9, 10). Additionally, a more detailed characterization of different AF patterns based on frequency, duration, and manner of conversion of AF episodes might further help to characterize the AF phenotype, although its predictive value for ablation success has not yet been described (11).

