## Discussion

Despite the advances in ablation techniques and the increasing knowledge of AF mechanisms, ablation outcomes remain relatively poor (4). Improved patient selection for invasive management and a graded choice for the type of ablation could help to enhance success rates and avoid unnecessary procedures and associated risks. In the multicenter, prospective ISOLATION cohort study, a range of possible predictors for ablation success is investigated. As AF is a multifactorial disease with numerous possible underlying mechanisms, predictors for successful treatment can be identified in several different domains. Combining recognized predictors with newer techniques that take different disease mechanisms into account may improve patient selection strategies. For this purpose, several established predictors within the clinical domain (e.g., age and comorbidities) are collected and complemented with possible predictors from investigational methods such as anthropometric information (15). Preprocedural AF patterns, while traditionally only described as paroxysmal, persistent, or longstanding persistent, are further specified toward a more detailed pattern description concerning the duration and frequency of the episodes. Echocardiography-derived information on cardiac anatomy will be supplemented with findings from cardiac CT or CMR. Non-invasive electrophysiological information will incorporate predictors derived from extECGs, in addition to those from the standard 12-lead ECGs. Biomarkers reflecting inflammation, prothrombotic state and endothelial dysfunction are measured and related to AF ablation success and common gene variants are scrutinized to determine the predictive value of an individual’s genetic background.

Keeping in mind the daily clinical practice, it would be desirable to implement a limited number of additional modalities to improve patient selection. Therefore, results from different examinations will be grouped and compared to determine the most suitable variable(s) and modalities for outcome prediction. Identifying these variables which hold the largest predictive value may help to tailor treatment strategy and timing to the individual patient.

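### No stated analysis shows whether a novel modality adds to the established predictors, because the plan neither keeps those predictors nor fits a model of them for comparison

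*Protocol article*

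**What the plan says.** The Introduction treats some characteristics as already known: "including demographic information, established clinical AF risk factors, and left atrial volume) have previously been identified as predictors for AF ablation success". It presents biomarkers, gene variants, surface-ECG features and detailed AF patterns as proposals whose value is still to be shown. The Abstract promises a model that combines the two kinds. The Discussion states the practical goal: "it would be desirable to implement a limited number of additional modalities to improve patient selection". The Conclusion likewise looks for the best combination of established predictors and novel techniques.

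The section Development of Prediction Model and Sample Size Calculation fixes the route:

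- **Screening.** In domains 1 to 5, "the three variables with the strongest correlation to ablation success are selected and presented to the model". Then "For subcategory 6 the two strongest predictors are used", and "The ablation technique that is chosen is used as a separate predictor".
- **Size.** "This approach leads to a total of 18 variables used to develop the multimodality model", and "a total of 180 events is required to conform to the rule-of-thumb to aim for 10 events per variable".
- **Selection.** Logistic regression with forward selection, AIC as the stopping rule. No variable is stated to be kept regardless.
- **Assessment.** The C-statistic and a comparison of observed frequencies across predicted-risk groups, for the whole cohort and by ablation strategy.

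The section gives its reason for not naming variables in advance: the newer techniques, "which each provide a multitude of possible variables of interest for which the predictive value has not been established".

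**The concern.** Choosing a limited number of additional modalities is a question of increment: what does a modality add to what the clinician already has? The fixed algorithm answers a different question, namely which mixture of screened variables fits best.

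Three features cause the gap. The clinical domain is capped at three places, although it holds demographics, comorbidities and body composition, and left atrial volume must win its place among the anatomical variables. Ranking by correlation with success takes no account of overlap between variables. Every stated performance measure describes the selected model, so there is nothing to subtract from it.

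A novel variable may therefore be retained by chance, or because it stands in for an established predictor that the screen removed. The stated outputs would not tell either case from real added value. The Discussion and Conclusion propose using the findings to select patients and tailor treatment, so a modality could be recommended on that basis.

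The reason given for not pre-specifying variables concerns new techniques of unknown value. It does not extend to predictors that the Introduction calls previously identified.

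**Working it through.** **1. The plan's own figures.** Variables: 5 × 3 + 2 + 1 = 18. Events: 18 × 10 = 180. Patients: 180 / 0.32 = 562.5, so 563. For 15% loss, 563 / 0.85 gives 663 and 563 × 1.15 gives 648; the target of 650 is close to both. At 650 enrolled: 650 × 0.85 = 552.5 evaluable, × 0.32 = 176.8 events, / 18 = 9.8 per variable. These figures reproduce. They count variables after screening and do not bear on added value.

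**2. How strict the AIC step is.** A one-coefficient term enters if twice the log-likelihood gain exceeds 2. For a single pre-specified variable with no effect, P(χ²₁ > 2) = 0.157. Screening hands AIC the best of many. With 5 independent useless candidates in each of five novel domains (25 in all), the chance that at least one passes is about 1 − 0.843^25 = 0.99.

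**3. Simulation of the written procedure.** The article does not give the candidate counts, so everything here is assumed:

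- 553 patients, about 32% events, 150 runs per setting.
- Eight established predictors, log odds ratio 0.3 per SD each: six in the clinical domain, AF type in domain 2, left atrial volume in domain 3.
- Novel candidates in domains 2 to 6 with no independent effect. In the last setting each had correlation 0.4 with the standardised sum of the established predictors.
- Screening 3/3/3/3/3/2, then forward AIC; ablation technique omitted; AUROC checked in 8,000 new patients.

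| Novel candidates per domain | Runs keeping ≥1 novel | Mean novel kept | Established passing screen (of 8) | Established kept | Apparent AUROC | New-patient AUROC |
|---|---|---|---|---|---|---|
| 5 | 99% | 3.9 | 5.0 | 4.9 | 0.715 | 0.644 |
| 10 | 100% | 6.3 | 4.9 | 4.8 | 0.732 | 0.635 |
| 20 | 100% | 8.6 | 4.8 | 4.8 | 0.746 | 0.625 |
| 50 | 100% | 10.8 | 4.6 | 4.6 | 0.766 | 0.610 |
| 20, proxies | 100% | 8.5 | 3.2 | 1.1 | 0.753 | 0.667 |

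The eight established predictors alone, without selection, gave an apparent AUROC of 0.720 to 0.724 and 0.702 to 0.703 in new patients.

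**4. Reading it.** All clinical candidates here were established, so three always passed. The remainder in the fourth data column is AF type and left atrial volume: 5.0 − 3 = 2.0 down to 4.6 − 3 = 1.6 of 2 when novel candidates were unrelated to them, but 3.2 − 3 = 0.2 of 2 when they were proxies. In new patients the selected model was worse than the reference in all five settings; its apparent AUROC was higher in four of the five. The selected model's own AUROC would not reveal this.

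**5. Overlap within a domain.** For three variables with common correlation r, 3 / (1 + 2r) gives an effective number of 1.9 at r = 0.3, 1.5 at 0.5 and 1.15 at 0.8. The correlations are assumed, and the formula concerns the variance of an average rather than predictive information. It shows only that three places need not hold three signals.

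**The case against.** The best defence is that the model is labelled exploratory, that the stated objective is to find predictors in six domains, and that added value appears only as a wish in the Discussion. Clinical variables enter the same forward selection, so a novel variable is admitted conditional on those already in the model. The Discussion also says that examinations will be grouped and compared to find the most suitable modalities, and an unseen analysis plan may say how. The model section uses left atrial volume index and AF type as examples for interaction testing, so the authors evidently expect them in the model.

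Much of this stands, and it rules out stronger readings that a reader might infer:

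- That the study cannot show added value. The data collected would permit a nested comparison; it is only not stated.
- That all domains have equal quotas. Genetics has two, and technique enters separately.
- That AUROC is the sole output. Observed risk groups and results by strategy are also planned.
- That the screen is certainly unadjusted. This is the natural reading of ranking by correlation, but the article does not use the word, and Statistical Considerations mentions both uni- and multivariable regression.
- That age, AF type and atrial size must crowd each other out. They would fall naturally in three different domains.

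The simulation is also open to challenge. Novel candidates were useless by construction, the reference model was the true one, and much of the gap between apparent and new-patient AUROC is selection optimism, a separate matter.

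What remains is that conditioning reaches only the established predictors that survived the screen, and that the planned comparison of modalities names neither method nor baseline. This is not mere silence, because the article does fix the selection algorithm and the performance measures.

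**Conclusion.** The point holds in limited form. The algorithm as fixed lets established predictors be screened out or dropped, and assesses only the selected model. No stated analysis therefore estimates what a novel modality adds to demographics, clinical risk factors and left atrial volume, and a novel variable's retention is not evidence that it adds anything.

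The direction is well supported: under assumed conditions, useless novel variables were retained in nearly every run. The size is not known. The AUROC differences depend on assumed effect sizes, candidate counts and correlations, and should not be read as a forecast for this cohort. The change is worth making before the analysis, because it determines what the study can conclude about modalities.

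**What to change.** Keep the planned exploratory model and add the following to the analysis plan:

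1. Pre-specify a compact reference model, fitted without selection: for example age, sex, the main clinical risk factors, AF type and left atrial volume, with ablation technique. AF type is proposed here; the Introduction does not list it among the known predictors.
2. For each novel domain, report the optimism-corrected change in C-statistic when it is added to the reference model. Repeat the screening and AIC steps inside every resample.
3. Label any likelihood-ratio test on screened variables as exploratory, since screening on the outcome invalidates its nominal p-value.

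The cost is analysis work and one results table. The reported gain from novel modalities may turn out smaller.

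Forcing the reference terms into the main model is a separate choice with a real price. Age, sex, six comorbidities from the pre-ablation work-up (hypertension, obesity, hyperlipidaemia, diabetes, COPD, sleep apnoea), AF type and left atrial volume make 2 + 6 + 1 + 1 = 10 terms. With technique that is at least 11 of 18, leaving at most 7 for the novel domains. A separate reference model avoids this.
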